#### Secondary endpoints

The change in average systolic and diastolic blood pressure during the day and the night, as assessed by 24-h blood pressure monitoring.The change in the rate at which blood pressure drops rate at night, as assessed by 24-h blood pressure monitoring.Assessment of target organ damage, using:
Heart rate variability, based on routine 24-h Holter recordings, which provide a sensitive and noninvasive measurement of autonomic input to the heart [14]The ankle-brachial index (ABI), which is the ratio of the systolic blood pressure (SBP) measured at the ankle to that measured at the brachial [15].Pulse wave velocity, which is the velocity at which the blood pressure pulse propagates through the circulatory system. It is calculated as the distance between the two arterial sites divided by the time delay for a pulse at the two sites [16].Assessment of any improvement in symptoms, using:
Hypertension Symptom Scale (Additional file 2)TCM Syndrome Integral Scale (Additional file 3)Pittsburgh Sleep Quality Index Scale [17, 18]Self-Rating Anxiety Scale [19]Self-rating Depression Scale [20]36-Item Short Form Health Survey, which assesses quality of life [21, 22]Blood lipids: Changes in levels of total cholesterol, triglycerides, low-density lipoproteins, and high-density lipoprotein will be assessed at baseline and treatment endpointSerum indicators of vascular function: Changes in serum levels of endothelin 1 (ET-1), thromboxane A2 (TXA2), NO, and prostaglandin I2 (PGI2) will be assessed at baseline and treatment endpointSafety indicators: Levels of creatinine, blood glucose, homocysteine, and uric acid, and routine blood and urine test will be assessed at baseline and treatment endpoint

### Laboratory tests

Levels of creatinine, blood glucose, blood lipids, homocysteine, and uric acid, plus routine blood and urine tests will be assessed at the Clinical Laboratory, China–Japan Friendship Hospital Beijing, China. Creatinine, blood glucose, blood lipids, homocysteine, uric acid, angiotensin II, and high-sensitivity C-reactive protein will be tested by an analyzer (Beckman Coulter Chemistry Analyzer AU5800, Beckman Kurt Co., Ltd., US). Blood will be tested by a blood analyzer (Sysmex Blood Routine Analyzer Xn90, SYSMEX Co., Ltd., Japan) and urine will be tested by a fully automated urine analyzer (AUTION MAX AX-4030, Aikolai Co., Ltd., Japan).

Blood samples will be sent to the Clinical Research Center of the China–Japan Friendship Hospital (transported at 2–6 °C) within 10 min of collection. After the blood is centrifuged, the supernatant fluid will be pipetted, stored in a cryotube, and placed in a freezer at −80 °C. The cryopreserved supernatant fluid will be tested using an enzyme-linked immunosorbent assay (ELISA) kit or chemical kit within 6 months to assess serum levels of ET-1, TXA2, and PGI2. Serum NO levels will be measured by the nitrate reductase method using a nitric oxide assay kit. The experimental procedure will be carried out by a professional technician following the manufacturers’ instructions. Instruments used during testing include an electronic balance (YP30001, Shanghai Guangzheng Medical Instruments Co., Ltd., China), a mini-shaker (MS1 Minishaker, IKA (Guangzhou) Instruments and Equipment Co., Ltd., China), a desktop low-speed automatic-balancing centrifuge (LDZ5–2, Beijing Jingli Centrifuge Co., Ltd., China), an electric constant-temperature water tank (HW. W21.600, Beijing Changfeng Instrument and Meter Company, China), and a multi-function microplate reader (SpectraMax M2, Meigu Molecular (Shanghai) Instruments Co., Ltd., China).

### Data collection and management

Data for each participant will be recorded in a case report form. In addition to the enrollment evaluation (−17 ± 0 days), each participant will attend an evaluation visit when allocated and every 14 days afterwards during the trial (0 days, 14 ± 2 days, 28 ± 5 days, 42 ± 5 days, and 56 ± 5 days). Each evaluation will include a physical examination, an assessment of any improvement in symptoms, an assessment of compliance with medications, questions about other medications, and questions about adverse events. Blood samples and 24-h blood pressure monitoring data will be collected only at the enrollment and close-out visits. Fig. 4 shows the schedule of enrolment, interventions, and assessments.

**Fig. 4 Fig4:**
[figure not shown]
Schedule of enrolment, interventions, and assessments

Data will be input into a clinical data management system through a website (http://www.cardiar.com/zryygxy) by two research staff. The system, which will be protected by passwords, will be managed by Beijing Cardiar Technology Co., Ltd. (Unified Social Credit Identifier 91110 10,655 68,170 240). All data supporting the conclusions of this trial will be stored in this system. To ensure data integrity and ease of storage, we will use data rules, valid values, and scope checks. The system will report missing data and data errors. The data may be changed but all changes will be tracked. The conduct of the trial will be audited by Beijing Inruida Pharmaceutical Technology Co., Ltd. (Unified Social Credit Identifier 91110105MA00H1U54L). These data management procedures will be undertaken completely independently of the investigators and the sponsor. All personnel involved in data entry and data management will sign a confidentiality agreement to prevent data leakage. The personal information of all participants will be fully protected. The original case report forms will be kept for 5 years after the end of the trial.

### Adverse events

Adverse events are defined as an accident, any signs of discomfort, or any disease symptoms, such as hypertensive emergencies, bleeding, hematoma, syncope, severe pain, and local infection. All details of adverse events that occur during the observation period will be recorded on the participant’s case report form. The clinical researchers must report each adverse event to the research leader, sponsor, and the ethics committee within 24 h. The ethics committee will recommend relevant treatment.

### Statistical analysis

#### Sample size calculation

The trial will check for superiority between group B (treatment with Losartan and placebo instead of SQG) and group C (treatment with SQG and Losartan), and for non-inferiority between group A (treatment with SQG and placebo instead of Losartan) and group B (treatment with Losartan and placebo instead of SQG).

The sample size was estimated based on clinical research literature and preliminary clinical data on blood pressure and FMD for hypertensive subjects. Given a type-I error rate of α=0.025 and a type-II error rate of β=0.1. The efficiency of the group C was estimated as 90%, and the group B as 70%. Superior efficiency cutoff is 10%. The calculation result was 78 patients in group B and group C by PASS 11 software. After considering the expulsion rate and the requirement of minimum case number of the GCP (A randomized controlled clinical trial requires at least 100 patients each group). We estimated 100 patients in group B and group C. Group A was an exploratory trail with the above two groups, 100 patients initially identified. Above all, we decided to recruit 300 patients during this trail.

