### Data analysis

Data entry and data management will be undertaken by an independent data administrator to ensure data accuracy. A professional statistician will perform the data analysis. We will use the intention-to-treat principle to analyze the efficacy and safety of SQG. For continuous variables, an independent two-sample Student’s *t* test will be used for comparisons between the two study groups, and a paired test will be used for intra-group comparisons. A χ^2^ test will be used for categorical variables. For continuous data with a normal distribution, a Wilcoxon test will be used. *P* < 0.05 is considered to be statistically significant, and all tests are two-tailed.

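### The 78 per group is reproduced only without the stated 10% superiority cutoff; against that cutoff, 100 per group gives about 45% power, where the design target is 90%

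*Protocol article*

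**What the plan says.** The Sample size calculation section of the protocol article sets up two comparisons: superiority of C over B, and non-inferiority of A to B. Only C versus B is sized; group A is described there as exploratory. The inputs are:

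- Error rates: "Given a type-I error rate of α=0.025 and a type-II error rate of β=0.1".
- Response rates: "The efficiency of the group C was estimated as 90%, and the group B as 70" per cent.
- Cutoff and result, one directly after the other: "Superior efficiency cutoff is 10%. The calculation result was 78 patients in group B and group C by PASS 11 software".

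The figure is then raised to 100 in each of groups B and C, to allow for an expulsion rate (no value given) and a stated minimum of 100 patients per group.

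The primary endpoint is efficiency, a responder outcome. The Data analysis section says "A χ^2^ test will be used for categorical variables", and that P < 0.05 "is considered to be statistically significant, and all tests are two-tailed". It does not mention the 10% cutoff.

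**The concern.** The cutoff stands among the inputs, immediately before the result, so a reader takes it that 78 per group gives 90% power to show that C exceeds B by more than 10 points. With an expected difference of 20 points, a 10-point cutoff halves the distance to be detected and so quadruples the sample size. A result of 78 looks far too small for that.

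The named test does not use the cutoff either. The article therefore carries two possible success rules for its only sized comparison: a difference above 10 points, or a difference above zero. They can give opposite answers on the same data. If the first rule applies, the trial fails more often than not even when its own assumptions are true. If the second applies, a significant result does not support a claim that the 10-point cutoff was exceeded. With both in print, the choice could be made after the results are seen.

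**Working it through.** **Inputs.** From the Sample size calculation section: p_C = 0.90, p_B = 0.70, α = 0.025, power 0.90, cutoff 10%, calculated n 78, planned n 100 per group. Allocation is 1:1 between B and C (Design section). I assume that:

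- α = 0.025 is one-sided, which agrees with the two-tailed 0.05 of the Data analysis section;
- 10% means 10 percentage points on C − B;
- 78 is per group;
- every randomised patient is evaluable.

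Alternatives to the first, second and fourth of these are tried below; the third is taken up with the objections.

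**Formula.** For a difference of two proportions tested against a cutoff δ, with unpooled variance:

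n per group = (z_α + z_β)² × [p_C(1 − p_C) + p_B(1 − p_B)] / (p_C − p_B − δ)²

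Here (1.960 + 1.2816)² = 10.507, and the variance term is 0.09 + 0.21 = 0.30. The numerator is 3.152.

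**Reproducing the plan's figure.**

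- δ = 0: 3.152 / 0.20² = 78.8 per group. Other zero-cutoff methods give 79 (arcsine) and 82 (pooled variance under the null). Power at 78 is 89.7% by the formula and 89.8% by exact enumeration of the chi-square test. The printed 78 belongs here.
- δ = 0.10: 3.152 / 0.10² = 315.2, so 316 per group. The Farrington–Manning score method gives 317.

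**Power at the sizes in the plan.**

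Power = Φ[(0.20 − δ)/√(0.30/n) − 1.960]

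| n per group | δ = 0.10 | δ = 0 |
|---|---|---|
| 78 | Φ(1.613 − 1.960) = 36.4% | 89.7% |
| 100 | Φ(1.826 − 1.960) = 44.7% | Φ(3.651 − 1.960) = 95.5% |

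Exact enumeration at 100 per group gives 44.4% for the Wald test against 10 points and 95.6% for the chi-square test of zero.

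**The two rules on one result.** Suppose the trial observes exactly 90% against 70% with 100 per group. The standard error is √(0.30/100) = 5.48 points, so the lower 95% limit is 20 − 1.96 × 5.48 = 9.3 points. That fails a 10-point cutoff. The chi-square statistic is 0.20² / (2 × 0.80 × 0.20 / 100) = 12.5 on 1 degree of freedom, far beyond the 5% critical value of 3.84. The same data fail one rule and clearly pass the other.

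**Other readings of the inputs.**

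- Cutoff relative to the 70% rate (7 points): 3.152 / 0.13² = 186.5, so 187 per group; power at 100 is 66%.
- α = 0.025 two-sided, 10-point cutoff: 373 per group; power at 100 is 33.9%.
- Weaker requirements, one-sided 0.05 and 80% power, 10-point cutoff: 186 per group, the smallest size found for a 10-point cutoff.
- Loss of patients (rates assumed, since none is given), 10-point cutoff: power is 41% with 90 evaluable per group and 37% with 80.

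None of these brings the required size near 78.

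**The case against.** The arithmetic is not in dispute. The objections concern what may be concluded from it.

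- **The 45% depends on a reading.** The article writes no null hypothesis or decision rule around the cutoff, and the only test it names for a categorical outcome addresses a zero difference. Under that test 100 per group is ample, at about 95%. This stands: 45% is the power if the cutoff is applied. It does not remove the inconsistency, because the cutoff is listed as an input to a figure it did not influence.
- **The plan does not claim 90% power at 100.** The β of 0.1 belongs to the calculated 78; the step to 100 covers losses and a minimum size. This is correct. The 90% is the design target, and against the cutoff neither 78 nor 100 reaches it.
- **Points, sidedness and full evaluability are assumptions.** They are, and the ranges are shown above. The relative reading raises power to 66%; a two-sided 0.025 or any loss of patients lowers it. No reading of the cutoff as a superiority margin yields 78.
- **That the cutoff was left out is inferred from a match.** The software inputs are not shown, so this stands. If 78 were a total of 39 per group, a score calculation with the cutoff's sign reversed would also give 39. The rise to 100 for each group favours the per-group reading, and on either reading the cutoff was not applied as stated.
- **The choice of hypothesis is the sponsor's.** Agreed; the remedy covers both choices.

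**Conclusion.** The concern holds and must be fixed. The printed inputs require about 316 per group, four times the printed 78, and 78 is in effect the answer for a cutoff of zero. At 100 evaluable patients per group and one-sided 0.025, power is about 45% against a 10-point cutoff and about 95% against zero. Across the alternative readings, with 100 evaluable, power against the cutoff runs from 34% to 66%, short of 90% throughout. If the chi-square test of zero difference is what is meant, the trial is adequately sized and the cutoff sentence is the error. If the cutoff is meant, both the sample size and the test are wrong.

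**What to change.** State one hypothesis for C versus B, and make the sample size, power and test follow from it, before the data are unblinded.

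- **Preferred, because it fits the planned size and test:** take the cutoff out of the hypothesis. State that C versus B tests a zero difference at two-sided 0.05, that 78 to 82 per group (depending on the formula) gives about 90% power, and that 100 evaluable per group gives about 95%. Keep 10 points only as a benchmark against which the confidence interval for C − B is read.
- **If the sponsor keeps the cutoff:** say whether it is in percentage points, replace the chi-square test with a test of H0: C − B ≤ 10 points (lower limit of the two-sided 95% interval above 10), and restate the power at 100 per group as about 45%. The 90% target would need about 316 per group.

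In either case, give the assumed loss rate so that power refers to evaluable patients. The cost is wording in the Sample size calculation and Data analysis sections, with no extra patients unless the sponsor wants both the cutoff and 90% power. The Trial status section reports 20 patients recruited at the time of writing, so at that point the rule could still be fixed early in the trial.

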### Data analysis

Data entry and data management will be undertaken by an independent data administrator to ensure data accuracy. A professional statistician will perform the data analysis. We will use the intention-to-treat principle to analyze the efficacy and safety of SQG. For continuous variables, an independent two-sample Student’s *t* test will be used for comparisons between the two study groups, and a paired test will be used for intra-group comparisons. A χ^2^ test will be used for categorical variables. For continuous data with a normal distribution, a Wilcoxon test will be used. *P* < 0.05 is considered to be statistically significant, and all tests are two-tailed.

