### Design

This study is a randomized double-blind double-simulation controlled trial. Participants will be recruited from the China–Japan Friendship Hospital through notices at the hospital and newspaper advertisements.

This clinical trial will recruit patients with stage I or II hypertension, and it will determine the efficacy and safety of SQG. All examinations and tests will be carried out according to the clinical trial plan. Participants will be randomized before the first treatment. Altogether, 300 subjects with stage I or II hypertension will be randomly assigned to three groups in a 1:1:1 ratio: group A (treatment with SQG and placebo instead of Losartan), group B (treatment with Losartan and placebo instead of SQG), and group C (treatment with SQG and Losartan) (Fig. 2). Recruited patients will receive an 8-week treatment (10 g of SQG or the placebo for SQG will be given twice a day in the morning and evening, and 50 mg of Losartan or the placebo for Losartan will be given every morning). SQG and its placebo are produced in China in accordance with the quality standards prescribed in the *Chinese Pharmacopoeia*
http://wp.chp.org.cn/front/chpint/en/. Upon completion of the 8-week treatment, follow-up tests will be conducted at weeks 2, 4, 6, and 8 after randomization.

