### Endpoint measurements

#### Primary endpoint

The primary endpoint is the difference in drug efficiency between the three groups. Efficiency is defined as:
Blood pressure is reduced to a threshold set out in *Guiding Principles for Clinical Research of New Chinese Medicines* [12].Flow-mediated dilation has increased by at least 2% [13].

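### Continuous secondary outcomes get an unadjusted t test, valid but less precise than ANCOVA on the baseline already collected, and within-group paired tests that cannot attribute a fall to the drug

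*Protocol article*

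**What the plan says.** The Data analysis section gives two tests for continuous variables. A two-sample Student's t "test will be used for comparisons between the two study groups, and a paired test will be used for intra-group comparisons". No baseline covariate is named.

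The outcomes that these tests serve are mainly the secondary endpoints. Blood pressure is worded as a change: "The change in average systolic and diastolic blood pressure during the day and the night, as assessed by 24-h blood pressure monitoring". Lipids and the serum vascular markers (ET-1, TXA2, NO, PGI2) are also worded as changes, and each "will be assessed at baseline and treatment endpoint".

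The timing is in Data collection and management: "Blood samples and 24-h blood pressure monitoring data will be collected only at the enrollment and close-out visits". The same section puts the enrolment visit 17 days before allocation; its sentence opens "In addition to the enrollment evaluation (−17 ± 0 days". Close-out is at day 56 ± 5. There is thus one pre-treatment and one post-treatment value per patient, and the pre-treatment value precedes allocation by 17 days.

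Under Design, "300 subjects with stage I or II hypertension will be randomly assigned to three groups in a 1:1:1 ratio". Group A takes SQG, group B Losartan and group C both, so no group receives placebo only.

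The primary endpoint is a responder rate compared across groups ("The primary endpoint is the difference in drug efficiency between the three groups"). It falls under the χ² test and is not at issue here.

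**The concern.** Two separate matters sit in one sentence of the plan.

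The first is efficiency. A t test on change subtracts the whole baseline value, whereas the best predictor of the close-out value uses only a fraction of it. The excess goes into the residual variance, so every continuous secondary comparison has less power than the same data could give.

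The second is attribution. A paired test asks whether the mean within an arm moved between enrolment and close-out. In patients enrolled because their blood pressure is raised, some fall is expected without any drug effect. With no placebo-only arm, the trial cannot show how large that fall is. A small P value from such a test does not separate the drug from regression to the mean or from change before treatment began.

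**Working it through.** **The plan's own figure.** The plan gives no power or precision figure for any continuous outcome, so there is none to reproduce. Its sample size rests on the binary primary endpoint. From it I take only the group size of 100: "We estimated 100 patients in group B and group C", with the same number for group A.

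**Step 1: precision of the between-group test.** Assume equal variance at baseline and close-out (set to 1) and a correlation r. The document gives no r, so I use 0.3 to 0.7.

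- t test on change: residual variance 2(1 − r)
- ANCOVA: residual variance 1 − r²
- Ratio: (1 − r²) / [2(1 − r)] = (1 + r)/2

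| r | Change, 2(1 − r) | ANCOVA, 1 − r² | Ratio | Variance saved | Power of t test on change where ANCOVA has 80% at 100 per arm |
|---|---|---|---|---|---|
| 0.3 | 1.40 | 0.91 | 0.65 | 35% | 62% |
| 0.5 | 1.00 | 0.75 | 0.75 | 25% | 68% |
| 0.7 | 0.60 | 0.51 | 0.85 | 15% | 73% |

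At r = 0.5, ANCOVA would need 75 patients for every 100 that the change-score t test needs.

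The direction does not depend on equal variances. If b is the slope of close-out on baseline, Var(change) − Var(ANCOVA) = (1 − b)² × Var(baseline). This is never negative, and it is zero only when b = 1.

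**Step 2: what the paired test picks up.** Let δ be the mean change that would occur without any drug effect and τ the drug effect in an arm. The paired test examines δ + τ. The randomised contrast examines (δ + τ₁) − (δ + τ₂) = τ₁ − τ₂, so δ cancels.

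For scale, assume an SD of change of 12 mmHg and n = 100. The standard error is 12/√100 = 1.2. With τ = 0, the chance of P < 0.05 for a fall is about Φ(δ/1.2 − 1.96):

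- δ = 2 mmHg: Φ(1.667 − 1.96) = Φ(−0.293) = 0.385
- δ = 3 mmHg: Φ(2.5 − 1.96) = Φ(0.54) = 0.705

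**Step 3: simulation of regression to the mean alone.** There were 5,000 trials per setting, with 100 per arm and no drug effect. Assumptions: entry limited to systolic pressure 140 to 180 mmHg on the analysed measurement; correlation 0.5 to 0.9; population mean/SD of 135/15, 145/12 or 150/12.

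- Mean within-arm fall: 0.4 to 7.6 mmHg across settings
- Paired test significant: 12% to 100% of null trials (58% at correlation 0.7, mean 145, SD 12)
- Between-group t test on change significant: 4% to 6%, its nominal level

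**Step 4: the pre-treatment interval.** From enrolment to close-out is 17 + 56 = 73 days, of which 56 are on treatment. Any change in the first 17 days is part of the paired difference.

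**The case against.** The defence has good ground on several points.

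- **A reader might infer that the between-group t test ignores baseline.** For 24-h blood pressure, lipids and serum markers it does not: Secondary endpoints defines them as changes, so baseline is used, though inefficiently. The larger saving against a t test on final values (1 − 0.91 = 9% at r = 0.3 to 1 − 0.51 = 49% at r = 0.7) therefore does not apply to them. It could matter only for outcomes not worded as changes, such as ankle-brachial index or pulse wave velocity, and only if final values are compared.
- **A reader might infer that regression to the mean biases the trial's group comparisons.** It does not. It cancels under randomisation, as Steps 2 and 3 show.
- **A reader might infer that within-group P values will be presented as proof that SQG works.** The document does not say so. It names the randomised comparisons, superiority of C over B and non-inferiority of A to B, and does not state how paired tests will be interpreted.
- **The size of the regression effect is uncertain.** The eligibility figure was not available for this check, so it is unknown whether patients are selected on the 24-h reading or on another measurement. Lipids and serum markers are not known selection variables. The 12% to 100% range shows how far the result follows the assumptions.
- **Covariate adjustment is often left to the analysis plan.** That is fair for an omission. Here, however, the article names the tests, so the stated method can be assessed.

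What remains is that the stated t test is less precise than a free alternative, and that the stated paired tests cannot carry a causal reading.

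**Conclusion.** The point holds as a modest one about secondary endpoints. The t test on change is valid; ANCOVA has 15 to 35% less variance at an assumed correlation of 0.3 to 0.7 with equal variances, and its variance is no larger at any correlation. The paired tests cannot attribute a fall to the drug, because patients are enrolled for stage I or II hypertension, every arm is active and the baseline predates allocation by 17 days. This is clearest for blood pressure; no single figure for its size can be drawn from the document.

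The primary endpoint, its χ² test, the sample size and the type I error of the randomised comparisons are untouched. The quoted text therefore gives no reason to add a model to the primary analysis.

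**What to change.** In Data analysis, replace the two-sample t test for each continuous secondary endpoint with ANCOVA of the close-out value on group and that endpoint's baseline value. Report the adjusted differences C-B and A-B with confidence intervals.

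Replace the paired tests with a descriptive report of within-group mean change and its confidence interval, without P values and without efficacy claims. State that the 24-h blood pressure and blood-sample baseline is the enrolment value.

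The cost is analysis wording only, since both values are already collected. Trial status reports 20 patients recruited at the time of writing, so at that stage the change could be made well before unblinding. The small downside is that within-group P values are dropped.

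### The stated rule for continuous data is reversed: normally distributed data are sent to the Wilcoxon test although the t test already covers them

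*Protocol article*

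**What the plan says.** All of the relevant text is in the Data analysis section of the protocol article.

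- Between groups: "For continuous variables, an independent two-sample Student’s" *t* "test will be used for comparisons between the two study groups". No condition on distribution is attached.
- Within groups: "a paired test will be used for intra-group comparisons", again without condition.
- By distribution: "For continuous data with a normal distribution, a Wilcoxon test will be used".
- Level: *P* "< 0.05 is considered to be statistically significant, and all tests are two-tailed".

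Categorical variables go to the χ² test. No other section modifies these sentences or mentions non-normal data.

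The Secondary endpoints section lists the outcomes that the rule governs. They include "The change in average systolic and diastolic blood pressure during the day and the night, as assessed by 24-h blood pressure monitoring", the nocturnal fall, heart rate variability, ankle–brachial index, pulse wave velocity, the symptom and quality-of-life scales, blood lipids, and the serum markers ET-1, TXA2, NO and PGI2.

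**The concern.** The t test is the usual choice for approximately normal data, and the Wilcoxon test is the usual alternative when normality is doubtful. The article ties Wilcoxon to normality instead. Two things follow from the literal text:

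1. A normally distributed outcome falls under both the general t-test sentence and the Wilcoxon sentence, so two analyses are prescribed for it.
2. A non-normal outcome falls only under the general sentence, so the t test is its default.

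A reader who compares the final report with this public protocol could not tell which test was planned for a normal outcome, because either choice matches one sentence. The endpoints concerned include the serum markers of vascular function, which bear directly on the first stated objective, endothelial dysfunction.

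**Working it through.** **Step 1: the sentences side by side**

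| Type of continuous outcome | General sentence | Distribution sentence | Result |
|---|---|---|---|
| Normal | t test | Wilcoxon | two tests, in conflict |
| Non-normal | t test | silent | t test by default |

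The error is in the wording, and the article gives no figure to reproduce. The calculations below only show how much it could matter.

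**Step 2: inputs**

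- From the article: 100 per group (Sample size calculation: "We estimated 100 patients in group B and group C"), and two-sided 0.05 (Data analysis).
- Assumed, because the article gives no SD or effect size for any continuous endpoint: a shift of about 0.4 SD. Skewed outcomes are taken as log-normal with log-SD 0.3 to 1.0, and the shift is applied on the log scale. For example, exp(0.4 × 1.0) = 1.49, a ratio of about 1.5.

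**Step 3: normal data**

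The asymptotic relative efficiency of Wilcoxon against the t test is 3/π = 0.955. In simulation (10,000 trials) power was 80.1% for the t test and 78.1% for Wilcoxon, a loss of 80.1 − 78.1 = 2.0 points.

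**Step 4: skewed data, power by simulation**

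| Log-SD (assumed) | t test | Wilcoxon | Loss with t test |
|---|---|---|---|
| 0.3 (ratio 1.13) | 79% | 79% | about 0 |
| 0.5 | 75.3% | 78.3% | 3.0 |
| 0.8 | 66.8% | 78.1% | 11.3 |
| 1.0 | 60.2% | 77.9% | 17.7 |

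The first row used 3,000 trials and the others 10,000. A separate run at log-SD 1.0 with a ratio of exactly 1.5 gave 62% and 79%, a loss of 17 points.

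The serum endpoints are changes from baseline, so change scores were also simulated, with an assumed baseline-to-follow-up correlation of 0.6. The pattern was the same:

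- log-SD 0.3: no gap;
- log-SD 0.5 (ratio 1.2): 77% against 80%;
- log-SD 0.8 (ratio 1.35): 70% against 81%;
- log-SD 1.0 (ratio 1.5): 67% against 85%.

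**Step 5: type I error**

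Used alone, each test rejected in 4.7% to 5.5% of null trials, for normal and log-normal data alike. If both tests were run on normal data and the smaller p-value kept, the rate was 5.9%.

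**The case against.** The strongest reply is that this is a slip of one word. A Wilcoxon sentence placed after a general t-test sentence makes sense only as the exception for non-normal data. The analysis is assigned to a professional statistician, and the full protocol (version 1.0) and any SAP are not at hand, so the slip may exist only in the article. This is probably the right account of the cause. It does not remove the point: the published rule is wrong as it stands, and nothing else in the article corrects it.

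The reply is right to limit the consequences. Four stronger readings are tempting, and the article does not support them:

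- **That the plan assigns skewed biomarkers to the t test.** It never mentions skewed data and does not say that any marker, lipid or scale is skewed. Non-normal data reach the t test only by default, and the skewness used above is an assumption.
- **That type I error rises to about 8%.** That rate arises when the better of two tests is picked for log-normal data. On the literal text only normal data have two tests, so the relevant figure is about 6%, and it too requires choosing after seeing the results.
- **That the results would be invalid.** At 100 per group both tests held their level in every case simulated.
- **That the primary endpoint is compromised.** Drug efficiency is a responder definition, planned as 90% against 70%, and belongs to the χ² test.

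**Conclusion.** The point holds as an error in a stated rule. The only distribution-based sentence in the analysis section is reversed and conflicts with the general sentence before it. The main cost is ambiguity over which test was planned for the continuous secondary endpoints, followed by some power.

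On normal data the literal rule costs about 2 points. On skewed data the cost runs from nothing to about 17 or 18 points, and its place in that range depends on log-SDs that the article does not give. The power figures also rest on the assumed shift of about 0.4 SD and, for change scores, on the assumed correlation. The text should be corrected, but the main conclusion of the trial does not depend on it.

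**What to change.** Rewrite the continuous-data sentences in Data analysis along these lines: *Approximately normal continuous outcomes will be compared between groups by the independent two-sample t test and within groups by the paired t test. Non-normal continuous outcomes will be compared between groups by the Wilcoxon rank-sum test and within groups by the Wilcoxon signed-rank test. The choice for each endpoint will be fixed before unblinding.*

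Inserting *non-* alone would put the Wilcoxon sentence right but leave the t-test sentence unconditional, so both need rewording. Which endpoints fall in which class can be left to the SAP. The cost is a few sentences of text, with no change to sample size, significance level or patient procedures. The Trial status section reports 20 of the planned 300 patients recruited at the time of writing, so the correction could be made well before unblinding.
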